### Baseline measures

A research assistant will assess the participants’ PSF by administering the validated Chinese version of FSS and the MFIS (52–55, 56). The FSS is the most frequently used tool to measure PSF (57–59) and consists of nine Likert items scored on a 7-point scale (e.g., “I am easily fatigued,” “My motivation is lower when I am fatigued than when I am not” and “Exercise brings on my fatigue”). A higher score on an item indicates the presence of greater fatigue, and the scores for all items are averaged to give a total fatigue score. In an assessment of the FSS in patients with neurological diseases, its Cronbach’s α was 0.90–0.94, its intraclass correlation coefficient was 0.73–0.93, and its correlation coefficients with other fatigue scales were 0.62–0.84, indicating that the FSS has good internal consistency, reliability and convergent validity in such patients (58). In addition, information on previous treatment of PSF will be collected using a questionnaire.

The MFIS is administered via a 5–10-min interview that assesses how fatigue affects people’s daily lives, in terms of their psychosocial, cognitive and physical functioning. The MFIS contains 21 items that are scored from 0 to 4, which represent different frequencies, i.e., “never,” “seldom,” “sometimes,” “often” and “always,” respectively. Subscores are obtained for cognitive functioning (0–36), physical functioning (0–40) and psychosocial functioning (0–8) and are summed to give a total score (0–84). A higher score indicates severer fatigue. The MFIS has been used to assess PSF (60) and measure outcomes in clincial trials of interventions for fatigue (61), including tDCS (37, 39, 62, 63).

A research assistant will use the Physical Activity Scale for the Elderly (PASE) (64), the Barthel Index (BI) (65), the MoCA, the anxiety subscale of the Chinese version of the Hospital Anxiety Depression Scale (HADSA), the Chinese version of the Geriatric Depression Scale (GDS), the Pittsburgh Sleep Quality Index (PSQI) (66) and the Chinese version of the Stroke-Specific Quality of Life (SSQoL) scale to, respectively, assess the participants’ level of physical activity, level of disability, global cognitive function, anxiety symptoms, depressive symptoms, sleep disturbances and health-related quality of life. The anxiety subscale of the HADSA consists of seven items, each of which is scored on a 4-point Likert scale, with higher scores representing severer anxiety. The Chinese version of the HADSA has been previously validated (67). The Chinese version of GDS contains 15 items, has a maximum possible score of 15, and has been previously validated (68). The PSQI measures seven components across 19 items, each of which is rated on a scale from 0 to 3, and the total possible score ranges from 0 to 21.

The Chinese version of the SSQoL scale (69, 70) is designed to measure quality of life in stroke survivors. It is a self-report questionnaire that contains 49 items covering 12 domains: family roles (three items), energy (three items), mobility (six items), language (five items), mood (five items), personality (three items), social roles (five items), self-care (five items), upper extremity function (five items), thinking (three items), work/productivity (three items) and vision (three items). Individual items are scored on a 5-point Likert scale representing answers from “completely true” to “not true at all,” with higher scores implying a better quality of life. Thus, the Chinese version of the SSQoL scale generates both domain and total scores. It has been previously shown to have excellent internal consistency, intertest reliability and test–retest reliability (69).

### Randomization and blinding procedure

A statistician will apply a block randomization procedure to afford a concealed randomization list. As mentioned, there with be 78 participants in each group (the sham tDCS group and the active tDCS group). Upon recruitment of each participant, the technician responsible for the tDCS delivery will receive information on the participant’s assigned treatment.

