## Methods

### Design

A double-blind randomized control trial of stroke survivors (Figure 1).

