### Intervention

A trained research assistant will administer tDCS at Shatin Hospital. The participants will recline on a comfortable chair with their eyes closed during tDCS, which will be delivered by one battery-driven constant-current stimulator (Soterix Medical 1 × 1 Clinical Trials Device) through one 5 × 5-cm conductive-rubber anodal electrode. The electrodes will be inserted into an EASYpad (Soterix Medical), which contains sponge material and will be moistened by application of approximately 10–15 mL of saline. The EASYpad will examined every minute to check whether additional saline needs to be added to prevent it from drying out. Each participant will be allocated a set of EASYpads that will be used for the entire treatment course to maintain good hygiene. Elastic straps will be used to fasten the EASYpad to the scalp. The anodal electrode will be positioned on the scalp over the C3 or C4 positions (motor cortex) of the lesioned hemisphere, based on the international electroencephalogram 10/20 system, and a cathodal electrode will be positioned on the ipsilateral shoulder (34) (Figures 2, 3). A constant current of 2 mA (with a current density of 0.08 mA/cm^2^) will be applied to the anode by one of the constant-current stimulators in two 20-min sessions, separated by a 10-min break (34), every day for 5 consecutive days. Sham tDCS will consist of 30 s of constant current at the beginning and end of each 20-min session, such that all of the participants will experience the initial itching sensation at the beginning of stimulation. The participants will be asked about skin sensations they experienced during and at the end of the stimulation to determine if they are able to distinguish between sham and real stimulation. The above stimulation site and parameters were chosen based on the following rationale. First, association observed between increased fatigue scores and decreased functional connectivity of supplementary and primary motor areas (42). In addition, stimulation of motor cortex has been shown to improve fatigue in stroke patients and healthy individuals (31, 71). Second, the duration of stimulation per session was 20 min in all five published studies of tDCS on PSF (42). Third, consecutive sessions of tDCS has been employed were employed in previous studies of tDCS on PSF (32, 34, 71).

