### Safety measures

The Adverse Event Checklist (AEC) will be administered at the end of each stimulation session. The AEC covers adverse events (AEs; symptoms) in various systems, namely, the circulatory, digestive, cardiovascular, musculoskeletal, metabolic, urogenital and nervous systems, and the whole body (72).

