### Withdrawal criteria

The participants should be able to complete the 10 sessions of tDCS treatment within 1 week. If they miss a scheduled session, they can receive another session when convenient. If the participants cannot complete the 10 sessions, they will be regarded as dropouts. In addition, participants will be removed from the study if they (i) withdraw their consent for tDCS treatment and/or (ii) have a severe AE that may lead to significant distressful consequences (seizure, skin burn or blister).

We will continue to follow withdrawn participants and perform outcome measures as far as possible.

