### Primary outcome measure

The MFIS will be administered before treatment (T0), after 10 treatment sessions (T1, 1 day after the fifth treatment day), and 1 week (T2), 2 weeks (T3) and 4 weeks (T4) thereafter (36), at the same time of day. The time window of administration will be adjusted to assess changes between time points (4 weeks for T0, 1 day for T1, 1 week for T2 and T3, and 2 weeks for T4). The participants and the research assistant who administers the MFIS will be blinded to the delivered treatment.

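### The person delivering tDCS is told the arm, and no blinded collector is stated for the adverse events and skin sensations gathered at those sessions

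*Protocol article*

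**What the plan says.** All references are to the Protocol article.

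- **Design:** "A double-blind randomized control trial of stroke survivors".
- **Randomization and blinding procedure:** once someone has been enrolled, "the technician responsible for the tDCS delivery will receive information on the participant’s assigned treatment". The deliverer therefore knows the arm.
- **Intervention:** on who gives the stimulation, this section says: "A trained research assistant will administer tDCS at Shatin Hospital". There are two 20-minute sessions a day for 5 days. On attendance during a session: "The EASYpad will examined every minute to check whether additional saline needs to be added". On the reporting of sensations: "The participants will be asked about skin sensations they experienced during and at the end of the stimulation". The stated purpose is to learn whether they can tell sham from real stimulation.
- **Safety measures:** "The Adverse Event Checklist (AEC) will be administered at the end of each stimulation session".
- **Withdrawal criteria:** apart from withdrawal of consent, the ground for removal is to "have a severe AE that may lead to significant distressful consequences (seizure, skin burn or blister").
- **Primary outcome measure:** "The participants and the research assistant who administers the MFIS will be blinded to the delivered treatment".
- **Table 1:** the tDCS adverse-effects questionnaire is marked at the treatment visits and at the end-of-treatment visit, where the MFIS is also taken.
- **Statistical analysis:** the safety analysis is descriptive and exploratory. It covers the incidence and intensity of adverse events and those leading to discontinuation. Withdrawals go into a logistic regression, and the per-protocol set holds only those who complete treatment.

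**The concern.** Disclosure of the arm to the operator is a stated design choice, not a detail left out of a condensed article. The two assurances of blinding cover the participant and the MFIS rater. They do not cover the operator, or whoever asks about sensations and gives the checklist. Both kinds of report are taken at the sessions the operator runs.

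Symptom reports depend partly on how they are asked for and recorded. Someone who knows the arm may probe more, or record milder complaints more readily, in active participants. Two results are exposed:

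- the comparison of adverse-event incidence and intensity between arms;
- the sensation question, which is the article's own check on whether the sham works. If the asker knows the answer, the check can be cued.

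The job titles add a second problem. If the research assistant who delivers tDCS were also the one who gives the MFIS, the blinding stated for the primary outcome could not hold. The article nowhere says that the two are separate people.

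**Working it through.** The plan gives no figure on this point, and its sample-size calculation does not bear on it. The check is therefore a comparison of sections, followed by a count and an illustration.

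**Step 1. Who does what, and whose blinding is stated**

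| Task | Person named | Blinding stated? | Section |
|---|---|---|---|
| Delivering tDCS | Technician | No: told the arm | Randomization and blinding procedure |
| Delivering tDCS | Trained research assistant | Not addressed | Intervention |
| Asking about sensations | Nobody named | No | Intervention |
| Giving the checklist after each session | Nobody named | No | Safety measures |
| Judging removal for a severe event | Nobody named | No | Withdrawal criteria |
| Giving the MFIS | Research assistant | Yes | Primary outcome measure |

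The first two rows give one task two titles. The second and last rows give one title to a task done with knowledge of the arm and a task done without it.

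**Step 2. Is the operator at hand when reports are taken?** The pad is inspected every minute, so someone attends throughout. Sensations are asked about during stimulation and at its end, and the checklist follows each session. It is a fair inference from timing that the operator is the person nearest. The text does not say that the operator asks.

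**Step 3. Exposure.** 2 sessions × 5 days = 10 checklists per participant. 10 × 156 participants = 1,560 planned administrations.

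**Step 4. Size.** The documents give no adverse-event rates and no recording sensitivities. What follows rests wholly on assumed values. Let the true incidence p be the same in both arms, and let the proportion of events recorded be s_A (active) and s_S (sham).

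Recorded difference = p × (s_A − s_S); recorded ratio = s_A / s_S.

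- p = 20%, s_A = 95%, s_S = 85%: 0.20 × 0.10 = 2 percentage points; ratio 0.95/0.85 = 1.12. With 78 per arm, 14.8 against 13.3 participants.
- p = 40%, s_A = 95%, s_S = 70%: 0.40 × 0.25 = 10 percentage points; ratio 0.95/0.70 = 1.36. With 78 per arm, 29.6 against 21.8 participants.
- s_A = s_S: difference 0.

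Under these assumptions the spurious difference runs from 0 to 10 percentage points. The range shows how the mechanism works and is not an estimate for this trial.

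**Step 5. Where it could reach.** Recorded adverse events feed the descriptive safety tables directly. Discontinuations attributed to adverse events would also alter the withdrawal regression and the per-protocol set, but only if discontinuation itself depended on knowledge of the arm. The documents do not show that it does.

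**The case against.** The strongest reply is that the article protects what matters most. Participants are blinded and report their own symptoms on a checklist. The sham delivers current at the start and end of each session. The rater of the primary outcome is blinded. Withdrawn participants are followed as far as possible, and anyone with at least one session stays in the intention-to-treat set. The safety analysis is descriptive. Who hands over a checklist is the kind of detail that a full protocol may settle, and research assistant may be a generic title for several people.

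Much of this stands, and it keeps the point modest. It does not remove it, because the operator's knowledge of the arm is stated outright and the titles conflict on the page.

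Four stronger readings are tempting, and the documents do not support them:

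- *The unblinded operator decides removals.* The Withdrawal criteria name no judge and no setting, and the listed events (seizure, skin burn, blister) are fairly objective.
- *The MFIS rater is unblinded.* The shared title leaves this open, but the article states the opposite.
- *Adverse-event questions come before the MFIS at T1 and reveal the arm.* Table 1 puts both at one visit. It fixes no order and does not say that one person gives both.
- *The double-blind label is false.* Blinding of participant and outcome rater is stated, and the label can be read in that sense.

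**Conclusion.** The point holds as a limited design weakness. The operator knows the arm. Blinding is stated only for participants and the MFIS rater. Adverse events and sensations are collected at the operator's sessions with no blinded collector stated. Recording of adverse events and the sham-versus-real check may therefore differ by arm.

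The size cannot be derived from the documents; the 0 to 10 percentage points above are assumed inputs carried through. The conclusion rests on one inference, that the operator is the likely collector because of the timing, and on the article being the only text at hand. A full protocol may name a separate, blinded collector. No bias in the primary outcome is shown. The change is worth making because it is cheap and because the stated blinding of the MFIS rater depends on a separation of roles that the article never states.

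**What to change.** 1. Give the operator only a per-participant code that sets active or sham, so that delivery needs no knowledge of the arm. This assumes that the stimulator accepts coded settings, which the article does not say.
2. If it does not, have participants complete the checklist and the sensation question themselves. Because any level of literacy is eligible, some will need the items read out, by someone other than the operator and the MFIS rater.
3. State that whoever delivers tDCS never administers the MFIS.
4. At T1, take the MFIS before the adverse-event questionnaire.
5. Reconcile the sections on randomization and blinding, intervention, safety measures, withdrawal criteria and primary outcome: one title for the deliverer, a named role for collecting adverse events and sensations, and a statement of who is blinded. For withdrawal, say only who makes the assessment and whether that person knows the arm. No change to the removal rule is proposed.

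The cost is wording, a code sheet and an emergency code-break to be kept. Separating deliverer and MFIS rater adds no staff if they are already two people, as the stated blinding requires. Reading items aloud in the fallback would take some extra staff time.

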### Intervention

A trained research assistant will administer tDCS at Shatin Hospital. The participants will recline on a comfortable chair with their eyes closed during tDCS, which will be delivered by one battery-driven constant-current stimulator (Soterix Medical 1 × 1 Clinical Trials Device) through one 5 × 5-cm conductive-rubber anodal electrode. The electrodes will be inserted into an EASYpad (Soterix Medical), which contains sponge material and will be moistened by application of approximately 10–15 mL of saline. The EASYpad will examined every minute to check whether additional saline needs to be added to prevent it from drying out. Each participant will be allocated a set of EASYpads that will be used for the entire treatment course to maintain good hygiene. Elastic straps will be used to fasten the EASYpad to the scalp. The anodal electrode will be positioned on the scalp over the C3 or C4 positions (motor cortex) of the lesioned hemisphere, based on the international electroencephalogram 10/20 system, and a cathodal electrode will be positioned on the ipsilateral shoulder (34) (Figures 2, 3). A constant current of 2 mA (with a current density of 0.08 mA/cm^2^) will be applied to the anode by one of the constant-current stimulators in two 20-min sessions, separated by a 10-min break (34), every day for 5 consecutive days. Sham tDCS will consist of 30 s of constant current at the beginning and end of each 20-min session, such that all of the participants will experience the initial itching sensation at the beginning of stimulation. The participants will be asked about skin sensations they experienced during and at the end of the stimulation to determine if they are able to distinguish between sham and real stimulation. The above stimulation site and parameters were chosen based on the following rationale. First, association observed between increased fatigue scores and decreased functional connectivity of supplementary and primary motor areas (42). In addition, stimulation of motor cortex has been shown to improve fatigue in stroke patients and healthy individuals (31, 71). Second, the duration of stimulation per session was 20 min in all five published studies of tDCS on PSF (42). Third, consecutive sessions of tDCS has been employed were employed in previous studies of tDCS on PSF (32, 34, 71).

**Figure 2 fig2:**
[figure not shown]
Demonstration of the setup on the arm.

**Figure 3 fig3:**
[figure not shown]
Demonstration of the setup on the scalp (C3).

### Safety measures

The Adverse Event Checklist (AEC) will be administered at the end of each stimulation session. The AEC covers adverse events (AEs; symptoms) in various systems, namely, the circulatory, digestive, cardiovascular, musculoskeletal, metabolic, urogenital and nervous systems, and the whole body (72).

### Withdrawal criteria

The participants should be able to complete the 10 sessions of tDCS treatment within 1 week. If they miss a scheduled session, they can receive another session when convenient. If the participants cannot complete the 10 sessions, they will be regarded as dropouts. In addition, participants will be removed from the study if they (i) withdraw their consent for tDCS treatment and/or (ii) have a severe AE that may lead to significant distressful consequences (seizure, skin burn or blister).

We will continue to follow withdrawn participants and perform outcome measures as far as possible.

### Primary outcome measure

The MFIS will be administered before treatment (T0), after 10 treatment sessions (T1, 1 day after the fifth treatment day), and 1 week (T2), 2 weeks (T3) and 4 weeks (T4) thereafter (36), at the same time of day. The time window of administration will be adjusted to assess changes between time points (4 weeks for T0, 1 day for T1, 1 week for T2 and T3, and 2 weeks for T4). The participants and the research assistant who administers the MFIS will be blinded to the delivered treatment.

### Secondary outcome measures

The FSS, the Chinese version of the GDS, the Chinese version of the HADSA, the PSQI, the BI and the PASE will be administered at T0, T1, T2, T3, and T4 (36), at the same time of day. The Chinese version of the SSQoL will be administered at T0 and T4. The time window of administration will be adjusted to assess changes between time points, as stated above. Data on the participants’ experience of, preferences for, and concerns and beliefs about tDCS will be collected at T4 via a brief questionnaire (33).

### Data monitoring body

An independent Data Safety Monitoring Board will be formed (DSMB) and will consist of a stroke neurologist, a psychiatrist, a statistician and a tDCS clinical trial specialist. The DSMB will meet regularly and examine AEs, perform an interim analysis and make recommendations on the safety of the study and the need to stop or extend the study.

### Sample size estimates

Statistical power was computed using Power Analysis & Sample Size 2005. We assumed that the standard deviation of the MFIS score at baseline will be 3.9 (60), that the sham stimulation will not cause any change in fatigue and that a decrease of at least 3.0 MFIS points will be clinically relevant (36). Hence, the effect size of tDCS will be (3.0/3.9 = 0.77). Given that such a large effect size is unusual in clinical contexts, we will instead use a more realistic effect size, i.e., 0.50. One pairwise comparison will be performed in the analysis of variance. A sample size of 63 per group (a total of 126 participants) will give rise to 80% power in identifying the main effect of tDCS (73). Thus, assuming a dropout rate of 20%, 156 (126/0.8) participants will be recruited.

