**Sample size estimates:**

We will recruit 156 participants aged 18 to 80 with chronic stroke and allocate them equally to two groups (i.e., *n* = 78 per group).

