### Statistical analysis

We will perform a per-protocol analysis and an intention-to-treat analysis. Only participants who complete treatment will be included in the per-protocol analysis, whereas all of the participants who receive at least one tDCS session will be included in the intention-to treat-analysis. A last-observation-carried-forward approach will be adopted for the analysis of outcome data. The mean score of the FSS will be calculated. The sum of individual item scores will be computed for the MFIS and the total score and physical, cognitive and psychosocial subscores will be derived. Demographic characteristics will comprise age, sex, and scores on the Chinese version of the GDS, the Chinese version of the HADSA, the PASE, the BI, the PSQI, and the NIHSS, and the severity of PSF will be measured using the FSS and the MFIS. Chi-square tests (for categorical variables such as sex) and t-tests (for continuous variables such as age) will be used to compare baseline performance. The effects of tDCS upon completion of treatment (T1) will be studied by entering the participants’ scores on the MFIS (total score and subscores) into a mixed-model analysis of variance with baseline MFIS scores as covariates, and the tDCS intervention (T0, T1) and stimulation (active, sham) as between-participant factors. The trend of tDCS effects will be studied by entering the participants’ scores on the MFIS (total score and subscores) into a linear mixed model with the tDCS intervention (T0, T1, T2, T3 and T4) and stimulation (active, sham) as within-participant factors. Pairwise comparisons between baseline and individual post-measurement-day significant results will conducted using Bonferroni t-tests for related samples. Withdrawals will be analyzed by logistic regression. The level of significance will be 0.05.

The safety analysis will be descriptive and exploratory. Key safety measures will be based on the tDCS AEs questionnaire and include the overall incidence and intensity of AEs; the number of AEs leading to treatment discontinuation; skin reactions; and other AEs.

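### The recruitment target is printed as 126/0.8 = 156, but the division gives 157.5 (158 in equal arms); at 20% dropout, 156 leaves 62.4 per group rather than 63, a slip worth about 0.4 points of power

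*Protocol article*

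**What the plan says.** The Sample size estimates section of the Methods first works out a large standardised effect and sets it aside as unusual: "we will instead use a more realistic effect size, i.e., 0.50". From that value it states that "A sample size of 63 per group (a total of 126 participants) will give rise to 80% power". It then allows for 20% dropout and gives the target, with its formula in brackets: "156 (126/0.8) participants will be recruited".

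The same number appears in two other places. The abstract says "We will recruit 156 participants aged 18 to 80 with chronic stroke", split equally, and the Randomization and blinding procedure section plans for "78 participants in each group". Under Statistical analysis, the significance level is fixed: "The level of significance will be 0.05". Whether the test is one-sided or two-sided is not stated.

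Two further passages bear on what the dropout allowance means. Withdrawal criteria counts as a dropout anyone who cannot complete the 10 sessions, and says that withdrawn participants will still be followed and measured as far as possible. Statistical analysis limits the per-protocol set to those who complete treatment. It places everyone with at least one session in the intention-to-treat set, and missing outcomes are carried forward from the last observation.

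**The concern.** The formula and its result stand side by side and do not agree. Dividing by 0.8 inflates the number of completers so that enough remain after losses. If the result is rounded down, fewer remain than the calculation called for. As printed, 156 recruited, 20% dropout and 63 completers per group are incompatible.

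The figure is the trial's headline size, used again in the abstract and in the randomisation section, so it is more than a stray typing error. The design also has no slack: 63 per group only just reaches 80% by the approximation that produces it. What is at stake is mainly whether a published sample-size justification can be reproduced from its own inputs, and only slightly the power itself.

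**Working it through.** **Inputs from the protocol article.** Standardised difference d = 0.50; power 80%; 63 completers per group, 126 in total; dropout 20%; equal allocation; target 156, shown as 126/0.8 (all from Sample size estimates, with the allocation also in the abstract). Alpha is 0.05 (Statistical analysis).

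**Assumption.** The test is two-sided. This reproduces the protocol's 63; a one-sided 5% test would need only 50 per group.

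**Step 1: reproduce 63 per group.** By the normal approximation, n per group = 2(1.960 + 0.842)² / 0.50² = 62.8, so 63. This matches. The t-based calculation gives 63.8, so 64. The protocol's 63 is therefore a normal-approximation figure, and that is the method by which to judge the slip.

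**Step 2: the dropout inflation.**
- In total: 126 / 0.8 = 157.5, so 158 in equal arms.
- Per arm: 63 / 0.8 = 78.75, so 79.
- Stated: 156, or 78 per arm. This is 2 short of 158 (2/158 = 1.3%).

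**Step 3: look for another route to 156.**
- Multiplying instead of dividing: 126 × 1.2 = 151.2, so 152.
- Starting from the t-based 64 per group: 128 / 0.8 = 160.
- Rounding 78.75 per arm down: 2 × 78 = 156. Of the routes tried, only this one gives the printed number.

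**Step 4: what 156 delivers.**
- At 20% dropout: 156 × 0.8 = 124.8, or 62.4 per group.
- Largest dropout that still leaves 126 completers: 1 − 126/156 = 19.2% (30 of 156).
- For comparison, 158 × 0.8 = 126.4, or 63.2 per group.

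**Step 5: power at d = 0.50, two-sided alpha 0.05.** The normal approximation is Φ(0.50 × √(n/2) − 1.960).

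| Completers per group | Normal approximation | t-test |
|---|---|---|
| 63 (stated) | 80.13% | 79.52% |
| 62.4 (156 at 20% dropout) | 79.75% | 79.13% |
| 62 (whole participants) | 79.50% | 78.87% |
| 63.2 (158 at 20% dropout) | 80.25% | 79.64% |

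Within either method, going from 63 to 62.4 costs about 0.4 points (80.13 − 79.75 = 0.38; 79.52 − 79.13 = 0.39). Rounding down further to 62 whole participants per arm makes the loss about 0.6 points.

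**The case against.** The best defence is that nothing of substance turns on this. The gap is 2 participants in 158, or 0.6 of a person per group. The 20% is a round planning assumption, and at 19.2% the printed target is sufficient. By the method behind the 63, power at 156 is 79.8%, which still rounds to 80%. The abstract, the randomisation section and the Methods agree with one another on 156. Dropouts, as the protocol defines them, stay in the intention-to-treat set once they have had one session, so the shortfall is mainly a per-protocol count.

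All of that stands and limits the size of the point. It does not make the printed division correct. No passage gives another dropout rate or a reason to round down. The sample-size section itself subtracts dropouts to reach its completer count, and the protocol plans both analyses without naming one as primary.

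A reader might infer something stronger: that the trial drops to about 79% power and loses roughly a full point. The documents do not support this. It compares a t-based 78.9% at 62 per arm with a nominal 80% that came from the normal approximation. On the t-test, 63 per arm already gives only 79.5%, so part of that gap comes from the choice of method and not from the division.

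**Conclusion.** The stated figure is wrong as written: 126/0.8 is 157.5, and equal arms need 158 (79 per group). At the protocol's own 20% dropout, 156 yields 62.4 completers per group instead of 63. The consequence is about 0.4 points of power, mainly in the per-protocol set. This is a point of the lowest severity.

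The arithmetic of the division rests on no assumption. The power figures assume a two-sided 5% test of two means at d = 0.50 with no gain from covariate adjustment, and dropout spread evenly over the arms. A reader might also infer that the trial is underpowered or must enrol two more people. Neither follows, because 156 is a workable target once it is described correctly.

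**What to change.** Keep 156 (78 per group) and correct the sentence in Sample size estimates so that it no longer equates 156 with 126/0.8. It could say that 156 recruits yield 126 completers (63 per group) if dropout is at most 19.2%, or about 62 per group and just under 80% power if dropout is 20%. It would help to add that the calculation is two-sided and uses the normal approximation, since that is what reproduces 63.

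This costs one line of text and a slightly less favourable stated dropout allowance or power. The abstract and the Randomization and blinding procedure section need no edit. They would change only if the sponsor chose to move the target itself to 158 (79 per group), which the size of the slip does not require.
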